## Abstract

**Background:**

Hearing loss is quite prevalent and can be related to people’s quality of life. To our knowledge, there are limited studies assessing the efficacy of hearing interventions on quality of life in adults. Therefore, we aim to conduct a randomized controlled trial (RCT) to determine the impact and cost-effectiveness of community-based hearing rehabilitation on quality of life among Chinese adults with hearing loss.

**Methods/design:**

In this two-arm feasibility study, participants aged 16 and above with some degree of hearing loss (*n* = 464) will be recruited from Linyi City, Shandong Province. They are randomly assigned to the treatment group or the control group. Those in the treatment group are prescribed with hearing aids, while those in the control group receive no intervention. Reinstruction in use of devices is provided for the treatment group during booster visits held 12 months post-randomization or unscheduled interim visits when necessary. Data are collected at baseline and the follow-up 20 months later. The primary outcome is changes in quality of life over a 20-month study period. Secondary outcomes include sub-dimensions in quality of life, physical functioning, chronic diseases, cognitive function, depression, social support, hospitalizations, falls, and healthcare costs. Finally, we will evaluate whether hearing aids intervention is cost-effective to apply in a large scale.

**Discussion:**

The trial is designed to evaluate the impact and cost-effectiveness of a community-based rehabilitation intervention on quality of life among Chinese adults with hearing loss. We hope that it would help improve the well-being for Chinese adults and provide references in policy and practice for China and other countries.

**Trial registration:**

Chinese Clinical Trial Registry ChiCTR1900024739. Registered on 26 July 2019.

**Supplementary Information:**

The online version contains supplementary material available at 10.1186/s13063-021-05228-2.

## Background

Hearing is one of the basic means of perception and communication. With the global aging, hearing loss is the most common sensory dysfunction and is becoming an increasingly serious public health issue [1]. It is said that more than 90% of the hearing loss is related to aging [2], most of which is irreversible [3]. In the USA, nearly two thirds of people over age 70 had hearing loss in 2015 [4]. In China, according to the Second National Sample Survey on Disability in 2006, the prevalence rate of hearing disability (mild or above) in older adults over 60 years old was about 11% [5], ranking the highest among six categories of disability (hearing, visual, language, physical, intellectual, and mental disabilities) [6].

Hearing loss can be associated with a series of health problems, such as poor physical and mental health [7, 8]. Empirical studies have shown that hearing loss is related to the decline in quality of life, presenting as more comorbid chronic diseases [9]; impaired physical functioning [3, 10]; more depressive symptoms such as sadness, despair, helplessness [9]; and accelerated cognitive decline [9]. The underlying mechanism may be that hearing loss impedes information exchange and social participation, which further impairs active physical functioning, increases psychological burden, and is associated with poor health [3, 10].

Although there is a strong correlation between hearing loss and health, it has not received enough attention from the public. First, hearing loss usually has a slow onset and gets worse progressively, which is difficult to detect in time unless by audiometry tests [11]. Our previous study proved that nearly half of the hearing-impaired people did not find themselves suffering from hearing loss or were not sure when the hearing loss occurred [12]. Second, a large number of people regard hearing loss as a natural aging process that can be disregarded [13]. What is more, the huge costs of hearing treatment like wearing hearing aids undoubtedly prevents the accessibility and utilization of rehabilitation services [14]. All these factors contribute to hearing loss becoming a widespread and undertreated health problem [13].

### The intervention of hearing aids use

The use of hearing aids is a main rehabilitation intervention for people with hearing loss [15]. One study investigating the predictors of rehabilitation intervention decisions in hearing-impaired middle-age and older adults found that hearing aids are more likely to be their first choice under most circumstances [16]. People who wear hearing aids have higher quality of life than those who do not, as evidenced by improved social skills, better self-care and mobility, lower levels of depression, and better overall health [17, 18]. But the accessibility and utilization rate of hearing aids are quite low [14]. Community-based surveys in developed countries have demonstrated that the use of hearing aids for older adults with hearing loss was around 10 to 20% from 1997 to 2005 [19–21]. Studies on hearing aids are scarce in developing countries [22]. Our study conducted in four provinces of China found that only 6.5% of the older adults with hearing loss had hearing aids in 2014 to 2015 [23].

Given the high prevalence of hearing loss and low accessibility of hearing aids, it is imperative to conduct high-quality studies to figure out the efficacy of wearing hearing aids. Systematic reviews on hearing and quality of life have found that a majority of studies were cross-sectional and only a few were conducted in developing countries [24]. Although there is a general consensus that hearing aids are beneficial for people with hearing loss, such as improving social function in Short Form 36 Health Survey (SF-36) [25], reducing risks of anxiety and depression in EuroQoL 5-Dimension (EQ-5D) [26], some studies suggest no evidence linking hearing aids use to improved quality of life [27, 28]. Besides, no randomized controlled trials (RCTs), to our knowledge, have studied the effects of hearing aids on exact health-related variables like depression, cognitive function, or service utilization in developing nations. Therefore, we supplemented these variables in our RCT as secondary outcomes to present more comprehensive quality of life outcomes, so as to add more compelling clinical evidence whether wearing hearing aids is cost-effective in developing countries like China.

In this protocol, we described the design of a randomized controlled trial to assess the impact and cost-effectiveness of hearing aids intervention on 20-month changes in quality of life. The study is expected to involve 464 Chinese adults aged 16 and older who have some degree of hearing loss and are required to wear a hearing aid by otologists. They are randomly assigned to the treatment group of wearing hearing aids or the control group with no intervention to determine the efficacy of hearing aids in improving the quality of life and to move toward early prevention and treatment of hearing loss.

### Objectives

The primary objective is to determine whether hearing aids intervention is effective in improving the quality of life in adults with hearing loss. The secondary objectives are to determine whether hearing aids treatment is cost-effective, including improving the health-related quality of life, decreasing inpatient and outpatient visits, and recovering productivity.

## Methods/design

### Study design, participants, and setting

Our study is a randomized, controlled trial lasting 20 months with two parallel groups, the treatment group and the control group. According to a list provided by the Hearing Center of Linyi Disabled Persons’ Federation, which records all the hearing-disabled people in Linyi City, 464 people are randomly selected. Participants are prescreened by telephone and complete a hearing screening at baseline (T0). Those in the treatment group are prescribed with hearing aids and receive a post intervention of reinstruction in use of hearing aids 12 months after T0, while the control group receives no interventions. The follow-up surveys are scheduled 20 months after T0 to trace changes in health outcomes (Fig. 1).

**Fig. 1 Fig1:**
[figure not shown]
Participants screening and randomization. Note: Strata defined by severity of hearing loss

### Eligibility criteria

Eligibility criteria are designed to identify community-dwelling adults with hearing loss who may possibly benefit from hearing rehabilitation (Table 1).

**Table 1 Tab1:** Inclusion and exclusion criteria

Criteria	Description
Inclusion	• Age 16 years old and above
	• Diagnosed with some degree of hearing loss and are required to wear a hearing aid
	• Plans to stay in the geographic area for study duration
	• Community-dwelling
	• Fluent Chinese speaker
Exclusion	• Inability to read or write
	• Cognitive, mental, language, or movement disability diagnosis
	• Self-reported use of a hearing aid in the past 1 year
	• Unwilling to wear hearing aids on daily basis
	• Medical contraindication to use of hearing aids (e.g., draining ear)
	• Conductive hearing loss with air-bone gap > 15 dB in two or more contiguous frequencies in both ears that cannot be resolved

To be included in the study, each person must meet the following inclusion criteria: Participants are adults aged 16 years and above with untreated bilateral hearing loss and are required to wear a hearing aid by otologists. Participants are community-dwelling and will remain in the local area during the study period. They should be fluent Chinese speakers.

Exclusion criteria include inability to read or write, prior cognitive, mental, language or movement disability diagnosis, medical contraindication to hearing treatment (e.g., draining ear), untreatable conductive hearing loss (difference in air audiometry and bone audiometry (“air-bone gap”) > 15 dB in two or more contiguous frequencies in both ears that cannot be medically resolved), or unwillingness to regularly wear hearing aids.

### Study interventions

Participants in the hearing treatment group are prescribed with hearing aids at baseline, while the control group with no interventions. Reinstruction in use of hearing aids is prescribed during booster visits held 12 months and 20 months post-randomization. Unscheduled interim visits may also be sporadically required (e.g., hearing aid malfunction). Participants in the control group will not have access to hearing aids. They will be asked to attend twice for this project: baseline and follow-up 20 months later.

### Modifications

Study participation and hearing intervention are expected to have a low risk of adverse events. But the age of the participants may naturally lead to certain deleterious health outcomes. In case of any accidental injury, lack of efficacy, or withdrawal of participant consent during the trial, investigators can modify or discontinue the trial with the approval of the principal investigator (PI).

### Adherence

Adherence to the study intervention will be assessed at each study visit using questions designed to capture adherence in both the treatment and control groups. Strategies to promote adherence include:
Individual assessment and instruction.Participants are asked to bring a communication partner with them to the study visits.Participants who miss a scheduled meeting are contacted by telephone by study staff to encourage continued participation and to evaluate and overcome barriers to participation.

For the treatment group, it additionally includes:
Potential intervention benefits are structured given the participant’s level of hearing loss in order to ensure that participants’ expectations are reasonable and realistic.Participants are informed that they are allowed to keep the hearing aids for free if they complete all study visits.

### Outcomes measures

#### Primary outcome

The primary study outcome is the 20-month changes in quality of life from the 2019 baseline to the 2021 follow-up. Quality of life can be measured by standard tests of Short Form 12 Health Survey (SF-12) [29] and EuroQoL 5-Dimension (EQ-5D) [30].

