#### Secondary outcomes

Key secondary outcomes include changes in sub-scores of SF-12 (physical and mental health) [29] and EQ-5D (mobility, self-care, usual activities, pain/discomfort, and anxiety/depression) [30]. Other secondary outcomes are health variables independently associated with hearing loss, including physical functioning (ADLs, IADLs) [31], chronic diseases, cognitive function (MMSE) [32], depressive symptoms (CES-D) [33], social support (LSNS) [34], hospitalizations, and falls, as well as the direct and indirect medical costs and loss of productivity in the study duration.

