### Sample size

Power calculations showed that 404 (202 in each group) participants are required in each group to obtain 80% statistical power with a 5% significance level and to detect a 0.28-SD difference in the mean change from baseline in quality of life score to 20-month follow-up [37]. To account for drop-in (uptake of hearing aids in the control group) and drop-out (discontinuation of hearing aid use in the treatment group), 464 persons are included, of which 232 are in the intervention group and 232 in the control group.

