### Data collection

Standardized data forms or tablets are used to collect data with paper back up available in case of tablet failure. Participants will fill in all questionnaires in a separate room. To ensure that appropriate help and guidance can be given when needed, one of the researchers will present. Meanwhile, communication partners who communicate with participants on a daily or near-daily basis (e.g., spouse) are often a key to getting accurate results. Therefore, accompanying adults are also invited to join the study and contribute to the data.

To minimize data-entry errors, the questionnaires have inbuilt check-and-skip rules. And the questionnaires were tested on four participants beforehand, who found the questions understandable and possible to complete in 30–45 min. For participants who withdraw from the trial, any data collected up to the withdrawal date will be retained and included in the analyses. Data are collected at the local field prior to randomization (baseline T0), after 12 months (post intervention T1) and 20 months after baseline (follow-up T2). A SPIRIT flow diagram illustrates the data collection in the intervention group and control group (Table 2) [38].

**Table 2 Tab2:** Schedule of enrollment, interventions, and assessments

Timepoint	Study period							
	Enrollment −T_1_ −30 to −1 day		Allocation T_0_ day 0		Post-allocation T_1_ 12 months		Close-out T_2_ 20 months	
	T ^a^	C ^b^	T ^a^	C ^b^	T ^a^	C ^b^	T ^a^	C ^b^
Enrollment								
Eligibility screen	×	×						
Informed consent	×	×						
Allocation			×	×				
Intervention			×		×		×	
Assessments								
Socio-demographic data	×	×	×	×			×	×
Hearing outcome								
Pure tone audiometry			×	×			×	×
HHIE-S score			×	×			×	×
Self-reported hearing			×	×			×	×
IOI-HA score					×		×	
Quality of life (primary outcome)								
SF-12 score			×	×			×	×
EQ-5D score			×	×			×	×
Secondary outcomes								
Sub-dimension of SF-12			×	×			×	×
Sub-dimension of EQ-5D			×	×			×	×
Physical functioning (ADLs)			×	×			×	×
Physical functioning (IADLs)			×	×			×	×
Chronic diseases			×	×			×	×
Cognitive function (MMSE)			×	×			×	×
Depression (CES-D)			×	×			×	×
Social support (LSNS)			×	×			×	×
Hospitalizations			×	×			×	×
Falls			×	×			×	×
Medical costs			×	×			×	×
Loss of productivity			×	×			×	×

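### The protocol puts two instruments under the primary outcome with no ranking or success rule but sizes the trial for one unnamed score, so the stated 5% and 80% cannot both be relied on.

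*Protocol article*

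**What the plan says.** The Primary outcome section gives one construct: "The primary study outcome is the 20-month changes in quality of life from the 2019 baseline to the 2021 follow-up". It then names two instruments for it: "Quality of life can be measured by standard tests of Short Form 12 Health Survey (SF-12) [29] and EuroQoL 5-Dimension (EQ-5D) [30". Neither is placed first.

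Table 2, in the Data collection section, has a block labelled "Quality of life (primary outcome)" with two rows under it, one for the SF-12 score and one for the EQ-5D score.

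The Secondary outcomes section places the components lower: "Key secondary outcomes include changes in sub-scores of SF-12 (physical and mental health) [29] and EQ-5D", followed by the five EQ-5D dimensions. What remains as primary is therefore an overall score from each instrument. The article does not say which overall scores these are.

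The Sample size section refers to a single score. The trial is planned "to obtain 80% statistical power with a 5% significance level". Its target effect is stated for one score only, the aim being "to detect a 0.28-SD difference in the mean change from baseline in quality of life score to 20-month follow-up". The score is not named. The Statistical analysis section specifies an analysis of covariance with multiple imputation for the intervention effect, with no ranking of the two scores, no success rule and no division of the 5%.

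**The concern.** A trial with two primary scores needs a rule for turning two results into one conclusion. There are three basic options: one score decides, either may decide, or both must succeed. Each has its own error rate and power, and the sample size section fits only the first. The Primary outcome section and Table 2 do not adopt that option.

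Two things are at stake. First, if the instruments disagree, the protocol gives no verdict on its primary objective. The Background makes disagreement plausible: it cites benefit on an SF-36 domain in one source, on an EQ-5D dimension in another, and no quality-of-life benefit in others. Second, the choice could be made after results are known. Participants and outcome collectors are unblinded, most data are self-reported, and the Data monitoring section lets the principal investigator act on interim analyses without saying which score they concern.

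**Working it through.** **Inputs from the Sample size section.** Difference 0.28 SD; significance level 5%; power 80%; 202 evaluable per group; 232 enrolled per group. The sentence "404 (202 in each group) participants are required in each group" repeats its last phrase. Since 202 + 202 = 404, I read it as 202 per group.

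**Assumptions.** Tests are two-sided. The correlation ρ between the two test statistics is not in the documents, so I use 0 to 0.8. For power, the true difference is 0.28 SD on both scores.

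**Step 1: the plan's own figure.** The normal approximation gives n = 2(1.960 + 0.842)²/0.28² ≈ 200.2, so 201 per group. The t-test version gives 201.2, so 202 per group and 404 in total, an exact match. A one-sided test would need 158 per group and does not match. The stated size is thus one two-sided test of one score at the full 5%.

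**Step 2: either score may win, each at 5%.** The false-positive rate is 1 − P(|Z₁| < 1.96 and |Z₂| < 1.96), with Z₁ and Z₂ standard normal with correlation ρ. At ρ = 0 this is 1 − 0.95² = 9.75%. Reporting whichever score gives the smaller p-value has the same rate.

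**Step 3: both scores must win, each at 5%.** The expected test statistic is 0.28 × √(202/2) = 2.814. Power is the bivariate normal probability that both statistics exceed 1.96, that is Φ₂(0.854, 0.854; ρ). At ρ = 0 this is 0.8034² = 0.646. The false-positive rate is at most 5%.

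| Assumed ρ | False-positive rate, either wins | Power, both must win (202 per group) | Per group for 80% power, both must win |
|---|---|---|---|
| 0 | 9.75% | 65% | 263 |
| 0.5 | 9.07% | 69% | 250 |
| 0.7 | 8.35% | 72% | 241 |
| 0.8 | 7.81% | 73% | 234 |

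**Step 4: both stay primary with the overall error rate held at 5%.**

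- *Fixed 2.5% for each score.* Power per score at 202 per group is 71% (t-test) to 72% (normal approximation). Power of 80% per score would need 243 per group (normal approximation).
- *Holm.* The smaller p-value is compared with 2.5% and, if that succeeds, the larger with 5%. Simulation at 202 per group gives:

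| Assumed ρ | Holm, power per score | Holm, power for at least one |
|---|---|---|
| 0 | 78% | 92% |
| 0.5 | 77% | 86% |
| 0.7 | 76% | 82% |
| 0.8 | 76% | 80% |

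**The case against.** The strongest reply is that the protocol nowhere says a result on either instrument is enough. It joins them with a plain conjunction under one construct, which could equally mean that both are required, and then the 5% is safe. That stands. A reader might infer that the error rate is nearly double its stated value, but the documents do not support this as a fact. It needs an either-wins rule or a choice made after the data are seen, and it also needs near-independence, which is unlikely for two general quality-of-life scores from the same person at the same visit. At a correlation of 0.8 the rate is 7.8%.

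A second reply is that this is a condensed article and a statistical analysis plan may exist. That stands for score construction and for the multiplicity procedure. It does not stand for the identity of the primary variable, because the article itself addresses that and does so inconsistently: two scores in the outcome section and schedule, one in the sample size. A later analysis plan cannot make a one-score calculation fit two primaries.

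A reader might also infer that the EQ-5D index has to be primary because of the economic objective. The article mentions no such index and does not tie the 0.28 SD to either instrument, so this is a reasonable choice and no more.

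Nor should the 232 enrolled per group be used to claim higher power at an undiluted 0.28 SD. The extra 30 per group are there to offset control uptake and discontinued use, which weaken the effect under intention-to-treat.

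**Conclusion.** The point holds in conditional form. The sample size arithmetic is correct for one score, and the defect is that the protocol designates two and gives no rule. If either can win, or the score is chosen afterwards, the two-sided false-positive rate is about 7.8% to 9.8% for correlations of 0.8 to 0, and it exceeds 5% at any correlation below 1. If both must win, the error rate holds and power at 202 per group is about 65% to 73% for correlations of 0 to 0.8.

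On either reading one of the two stated design figures fails. Which one fails cannot be told from the article. The ranges rest on assumed correlations and on a 0.28-SD effect on both scores. The existence of the gap rests on neither. It should be settled before analysis because it decides what the trial's main conclusion means.

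**What to change.** Before any outcome data are examined, amend the Primary outcome section and Table 2 to name one overall score as the single primary variable. State in the Sample size section that the 0.28-SD difference refers to that score, and justify it for that instrument. Move the other instrument to key secondary. The 202 evaluable and 232 enrolled per group then stand. EQ-5D is one reasonable choice given the cost-effectiveness objective.

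If both instruments must stay primary, state the success rule, hold the overall error rate at 5% (for example by Holm) and restate the power. At 202 per group with 0.28 SD on both scores, Holm gives about 76% to 78% per instrument and about 80% to 92% for at least one, for correlations of 0.8 to 0. A fixed 2.5% split gives about 71% per instrument.

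The cost is a short amendment and no new data. One instrument loses primary status, and the Ethics approval and protocol amendments section requires IRB approval before the change takes effect. Recruitment ended in July 2019 and the trial is unblinded, so the amendment should record that the choice was made without sight of outcome data, including any interim analysis.
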